# Vestibular prognosis in idiopathic sudden sensorineural hearing loss with vestibular dysfunction treated with oral or intratympanic glucocorticoids: a protocol for randomized controlled trial

**DOI:** 10.1186/s13063-020-04579-6

**Published:** 2020-07-22

**Keywords:** Randomized controlled trial, Vestibular function, Sudden hearing loss, Glucocorticoid

## Abstract

**Background:**

Idiopathic sudden sensorineural hearing loss (ISSNHL) is a rapid-onset sensorineural hearing impairment with unclear etiology and unsatisfying treatment effects. Vestibular dysfunction has been considered as a poor indicator in the clinical manifestations and prognosis of ISSNHL, which occurred in approximately 28–57% cases. Glucocorticoids, administered through oral or intratympanic way, are currently regularly and standardly applied for ISSNHL to improve the hearing outcome. However, the vestibular prognosis of ISSNHL after routine treatments remains seldom explored. This study aims to compare the effectiveness of oral and intratympanic glucocorticoids in ISSNHL with vestibular dysfunction in terms of the pattern and trajectory of possible process of vestibular function recovery.

**Methods/design:**

A randomized, outcome-assessor- and analyst-blinded, controlled, clinical trial (RCT) will be carried out. Seventy-two patients with ISSNHL complaining of vestibular dysfunction appearing as vertigo or imbalance will be recruited and randomized into either oral or intratympanic glucocorticoid therapy group with a 1:1 allocation ratio. The primary outcomes will be vestibular function outcomes assessed by sensory organization test, caloric test, video head impulse test, cervical vestibular evoked myogenic potential, and ocular vestibular evoked myogenic potential; the secondary outcomes include self-reported vestibular dysfunction symptoms; dizziness-related handicap, visual analogue scale for vertigo and tinnitus; and pure tone audiometry. Assessments of primary outcomes will be performed at baseline and at 4 and 8 weeks post-randomization, while assessments of secondary outcomes will be performed at baseline and 1, 2, 4, and 8 weeks post-randomization.

**Discussion:**

Previous intervention studies of ISSNHL included only hearing outcomes, with little attention paid on the prognosis of vestibular dysfunction. This trial will be the first RCT study focusing on the progress and prognosis of vestibular dysfunction in ISSNHL. The efficacy of two commonly used therapies of glucocorticoids will be compared in both auditory and vestibular function fields, rather than in the hearing outcome alone.

**Trial registration:**

ClinicalTrials.gov NCT03974867. Registered on 23 July 2019

## Background

Sudden sensorineural hearing loss (SSNHL) is a rapid-onset inner ear disease. It is defined as a sensorineural hearing loss of at least 30 dB over at least three test frequencies occurring within 72 h [1, 2]. The reported incidence rate of SSNHL is about 5–27/100,000 people per year [1], which has been widely considered underestimated because of the unregistered cases with out-of-hospital spontaneous recoveries. The etiology in about 71 to 90% of SSNHL cases remains uncertain, which is defined as idiopathic SSNHL (ISSNHL) [1, 3]. Various postulated etiological theories have been proposed including microvascular impairment, viral infections, inner ear electrolytic disorders, trauma, autoimmune diseases, and central nervous system (CNS) diseases [3–7]. Based on the close anatomic relationship between cochlea and vestibule, approximately 28–57% of ISSNHL patients have also reported of co-occurring symptoms of vertigo [8].

There are two administration patterns of glucocorticoids for ISSNHL: systemic (oral or intravenous) and intratympanic therapies. Compared with the traditional oral administration, intratympanic therapy is thought to be superior for its (1) bypassing the blood-labyrinth barrier and achieving higher drug concentrates in the inner ear and (2) avoiding most of the systemic side-effects of glucocorticoids. A well-designed randomized trial was conducted in 2011 by Rauch and his colleagues, which supported the non-inferiority in hearing outcomes of intratympanic therapy compared with oral prednisone in ISSNHL. However, the study was failed to reject the inferiority based on the 10-dB non-inferiority standards in the subgroup analysis of ISSNHL with dizziness [9].

Considering that few investigations have been carried out on progress and prognosis of ISSNHL-related vestibular dysfunctions after basic treatment, we designed this randomized, assessor- and analyst-blinded, controlled trial with two interventional arms, one is the oral glucocorticoid therapy group and the other one is the intratympanic glucocorticoid therapy group. Our research hypothesis is that intratympanic methylprednisolone is superior to oral prednisone on vestibular function recovery of ISSNHL patients with vertigo.

## Methods/design

### Study design and settings

This protocol is reported in accordance with the *Standard Protocol Items: Recommendations for Interventional Trials guidelines* (*SPIRIT*) (Additional file 1) [10]. This study is designed as an 8-week, single-center, randomized, assessor- and analyst-blinded, controlled trial with two parallel interventional groups in a 1:1 allocation. Patients will be recruited from outpatient clinics of the Eye and ENT Hospital of Fudan University in Shanghai, qualified with well-trained doctors, staff, and required facilities for this clinical trial.

### Participants

Patients who meet all of the following inclusion criteria will be considered eligible:
Adults aged between 18 and 70 years old;Diagnosed with unilateral ISSNHL according to the National Institute for Deafness and Communication Disorders (NICDC) criteria [2];Complained of vertigo/imbalance together with abnormal results in at least one of the vestibular function tests, including sensory organization test (SOT), caloric test, video head impulse test (vHIT), cervical vestibular evoked myogenic potentials (cVEMP), and ocular vestibular evoked myogenic potentials (oVEMP);Onset of audio-vestibular symptoms occurred within 7 days; andBe willing to sign the informed consent of the study.

Patients with any of the following conditions will be excluded:
Definite etiologies are found or highly suspected after clinical evaluations, such as vestibular schwannoma, stroke, trauma, or demyelinating disease;Diagnosed with a present or previous hearing or balance disorders, such as Meniere’s disease, benign paroxysmal positional vertigo, vestibular neuronitis, vestibular migraine, otosclerosis, luetic, and congenital or genetic hearing loss;Pure tone audiometry (PTA) threshold of the unaffected ear is higher than 25 dB;Present with conditions contraindicated systemic glucocorticoid use, such as tuberculosis, hepatitis B or C infection, active herpes zoster infection, pancreatitis, insulin-dependent diabetes mellitus, severe osteoporosis, or gastrointestinal ulcer;A history of more than 3 days sufficient systemic glucocorticoid uses (≥ 1 mg/kg/day) within 3 months;Not appropriate for receiving vestibular function tests;Multiple organ dysfunction or unstable vital signs;Pregnancy or lactation; andUnsuitable for the trial because of any other reasons identified by investigators.

### Recruitments and randomization

Patients who visit doctors from the outpatients and suspected of ISSNHL with vestibular dysfunction will be screened for eligibility. Eligible patients who consent to participate will receive either oral prednisone or intratympanic methylprednisolone randomly in a 1:1 allocation. The randomization sequence will be generated [contact], an internet website (https://www.random.org) producing true random sequence according to atmosphere noise. The concealed randomization sequence file will be constructed and kept in sequentially numbered, sealed, opaque envelopes by a staff member ([name]) in the Eye and ENT Hospital of Fudan University outside the study team. All the potential participants will be evaluated in strict chronological order of visiting time. When a patient is officially enrolled and numbered, the staff member will be contacted by telephone and open the corresponding envelope to find the randomized treatment for this patient. Assessors in examination rooms and statistician analysts are not allowed to receive any information of the group allocation. The information of participants will be referred using research code among investigators, and their personal information (like name and contacts) will be kept confidential before, during, and after the trial.

Following randomization, baseline information of the participants in demographic and clinical characteristics will be collected, such as age, gender, nationality, occupation, date of onset, predisposition, initial symptoms, time of diagnosis, any treatments before enrolments, body mass index (BMI), and comorbidities. The objective vestibular function evaluated by SOT, videonystagmography (VNG), vHIT, cVEMP, and oVEMP and the hearing outcome assessed by PTA will be performed at baseline and at 4 and 8 weeks after randomization, while the subjective vestibular dysfunction feelings reflexed by dizziness handicap inventory (DHI) and visual analogue scale for vertigo (VAS-V) and the tinnitus condition assessed by VAS in tinnitus (VAS-T, visual analogue scale for tinnitus) will be performed at baseline and at 1, 2, 4, and 8 weeks after randomization. Caloric test is routinely included in VNG. Acoustic impedance and magnetic resonance imaging of the internal auditory canal (MRI-IAC) will be performed only once at the baseline examination to exclude the potential misdiagnosed SSNHL.

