### Interventions and comparisons

Once a participant is randomized, the treatment procedure starts immediately (Table 1). The participants in group 1 will receive oral prednisone 1 mg/kg/day (maximum daily dosage is no more than 60 mg) for 7 days, followed by a 7-day taper (Table 1). The patients are advised to take the medicine in 30 min before every breakfast, and not to divide the doses. The participants in group 2 will receive 7 intratympanic 40 mg/ml methylprednisolone injections in 14 days, one injection every other day.

**Table 1 Tab1:** Glucocorticoid therapy protocol in each group

	Drug	Protocol
Group 1	Pred.	Glucocorticoid therapy: d1–d7: Oral Pred. 1 mg/kg/d (maximum daily dosage is no more than 60 mg) d8–d9: Oral Pred. 10 mg less than d7 d10–d11: Oral Pred. 10 mg less than d9 d12: Oral Pred. 10 mg less than d11 d13: Oral Pred. 10 mg less than d12 d14: Oral Pred. 10 mg less than d13^a^
Group 2	Met.	Glucocorticoid therapy: One intratympanic injection of 40 mg/ml Met. at d1, d3, d5, d7, d9, d11, and d13;^b^

Pred. prednisone, Met. methylprednisolone, d. day

^a^If the patient’s weight is less than 50 kg, the administration will be stopped after the day with < 10 mg prednisone administered, for example, a patient weighs 45 kg will stop receiving glucocorticoids at the 13th day

^b^One day early or late of injection is allowed for practicality

The otolaryngologists in charge of the injection work are asked to inject at the posterior superior quadrant and fulfill the tympanic cavity using operating microscopes, after lidocaine spray anesthesia. Patients will be asked to keep supine position with the affected ear slightly up to 30° and avoid swallow during injection and in 30 min after the injection. The drug for injection is methylprednisolone sodium succinate for injection by Pfizer Manufacturing Belgium NV.

Of all the participants, the length of treatment would be extended for another week if the change in hearing threshold (average dB in PTA) is less than 10 dB, or average of PTA is worse than 55 dB in the patient’s affected ear, under the participant’s agreement. The salvage treatment regimen is 3 injections of 40 mg/ml methylprednisolone every other day. Records and effects of the salvage treatments will be reported in the study results and evaluated according to both intention-to-treat (ITT) and per-protocol analyses. For those with severe vertigo attacks, drugs for symptom control like mannitol or diazepam can be used temporarily.

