#### Secondary outcomes

Secondary outcomes include the change of subjective evaluations in vestibular, tinnitus, and hearing assessments:
Change of DHI and VAS-V, VAS-T scores: change of DHI and VAS-V scores from baseline at 1-, 2-, 4-, and 8-week follow-up.Change of PTA: change of average of PTA from baseline at 1-, 2-, 4-, and 8-week follow-up; in this study, we define a 10-dB PTA criterion as clinically significant difference based on a previous RCT [9].Safety: rates of study-related adverse events (AEs), such as short-term systemic use of glucocorticoids related SAEs and AEs, and intratympanic injection-related AEs.

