### Time points

The study included 5 follow-up visits in total: a baseline visit to sign the consent and to record the baseline information, 2 visits during treatment interval to record subjective vestibular questionnaires (DHI, VAS-V, and VAS-T) and hearing outcomes (PTA) and to monitor treatment safety outcomes, and 2 follow-up visits at 4 weeks and 8 weeks to assess hearing and vestibular functions and monitor safety outcomes. To optimize examination resources and reduce burden of examiners, among all five vestibular function tests (SOT, caloric test, vHIT, cVEMP, and oVEMP), only those with previous abnormal results will be repeated at follow-up visits.

The study flow diagram is shown in Fig. 1, and the SPIRIT figure of enrolment, interventions, and assessments is presented in Table 3.

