### Blinding

We decide not to set blindness of the interventions to patients and doctors, because that setting blindness to patients and doctors will need placebo injections to some of the participants, which may bring unnecessary pain and tympanic membrane perforation risk to the patients. The specialists in test rooms and statistical analysts will be kept blinded during the trial until the statistical analyses are done.

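### The plan places baseline recording after randomisation in an open-label trial that treats at once, so self-reported baseline scores may be taken with the arm already known

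*Protocol article*

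**What the plan says.** All references are to the protocol article.

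- **Recruitments and randomization, allocation.** Once a patient is enrolled and numbered, "the staff member will be contacted by telephone and open the corresponding envelope to find the randomized treatment for this patient".
- **Recruitments and randomization, next paragraph.** "Following randomization, baseline information of the participants in demographic and clinical characteristics will be collected". The items named include demographic facts, date of onset, initial symptoms, earlier treatment, BMI and comorbidities. The next sentence gives the schedule of the vestibular tests and PTA, and then says that the self-reported scores (DHI, VAS-V, VAS-T) "will be performed at baseline and at 1, 2, 4, and 8 weeks after randomization".
- **Interventions and comparisons.** "Once a participant is randomized, the treatment procedure starts immediately". Table 1 puts the first tablet or injection on day 1.
- **Blinding.** "We decide not to set blindness of the interventions to patients and doctors". Test-room specialists and analysts are blinded.
- **Secondary outcomes.** These include "change of DHI and VAS-V scores from baseline at 1-, 2-, 4-, and 8-week follow-up"; the item's heading also names VAS-T.
- **Participants.** Entry requires "abnormal results in at least one of the vestibular function tests".
- **Time points.** There is "a baseline visit to sign the consent and to record the baseline information", with no order given relative to randomisation.

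**The concern.** A baseline value serves as a reference only if allocation cannot have influenced it. Here the stated order is allocation first and baseline information second, in a trial where the patient learns the arm and starts treatment straight away. For DHI, VAS-V and VAS-T the patient is the assessor, so blinding the test rooms does not protect them.

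If knowing the arm, or having had the first dose, shifts the baseline score in one arm, every later change from baseline in that arm carries the shift. The Adverse events section offers one route: it lists worse vertigo as a possible event after injection, which concerns one arm only. A symptom score taken after a day-1 injection could therefore be raised in that arm and later read as greater improvement. That is the direction the Discussion expects. Doctor-recorded initial symptoms are exposed in a similar way.

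At stake are the self-reported secondary outcomes at weeks 1, 2, 4 and 8, and the credibility of the baseline symptom history.

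**Working it through.** **Step 1: order of events, item by item**

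| Item | What the text fixes | Can allocation influence it? |
|---|---|---|
| Vestibular tests | Needed for entry, so before randomisation; blinded assessors | Largely no |
| PTA | Needed for the diagnosis and for the unaffected-ear criterion; blinded examination rooms | Largely no |
| MRI and acoustic impedance | At the baseline examination, to rule out misdiagnosis | Largely no; objective |
| Age, BMI, date of onset, comorbidities | After randomisation, as stated | Hardly; fixed or historical |
| Initial symptoms, earlier treatment | After randomisation, as stated | Initial symptoms yes; earlier treatment less so |
| DHI, VAS-V, VAS-T | At baseline; same paragraph; not placed before allocation | Yes, if taken after the envelope is opened |

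The paragraph cannot be a strict chronology throughout, because the vestibular tests it lists must precede randomisation. It nevertheless states a post-randomisation order for the history and leaves the self-reported scores unplaced. Neither the eligibility criteria nor the Time points section settles where those scores fall.

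**Step 2: how a shift would pass into the result**

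The plan gives no figure on this point, so there is none to reproduce. Let *d* be a between-arm baseline difference (in SD) caused only by knowing the arm, *r* the baseline/follow-up correlation, and *n* the number per arm. Assume equal SDs, no true effect, and a shift at baseline only.

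- Change score: bias = *d*; SE = √(2(1 − *r*)) × √(2/*n*)
- Baseline-adjusted: bias = *r* × *d*; SE = √(1 − *r*²) × √(2/*n*)
- Two-sided false-positive rate: Φ(−1.96 − bias/SE) + 1 − Φ(1.96 − bias/SE)

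The only input from the document is *n* = 36 (Sample size and statistical methods). The values of *d* and *r* are assumptions.

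Example with *d* = 0.2 and *r* = 0.5: √(2/36) = 0.2357.

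- Change score: SE = 1 × 0.2357, bias/SE = 0.849, rate 13.6%.
- Adjusted: SE = 0.866 × 0.2357 = 0.2041, bias = 0.1, bias/SE = 0.490, rate 7.8%.

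False-positive rate at a nominal 5%, 36 per arm:

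| Shift *d* | Change, *r* = 0.3 | 0.5 | 0.7 | Adjusted, *r* = 0.3 | 0.5 | 0.7 |
|---|---|---|---|---|---|---|
| 0.1 SD | 6.5% | 7.1% | 8.5% | 5.2% | 5.7% | 7.0% |
| 0.2 SD | 11.1% | 13.6% | 19.5% | 5.8% | 7.8% | 13.2% |
| 0.3 SD | 18.9% | 24.7% | 37.6% | 6.9% | 11.4% | 23.9% |
| 0.5 SD | 43.4% | 56.4% | 78.2% | 10.2% | 23.2% | 54.8% |

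Adjustment reduces the bias but does not remove it. The table shows sensitivity to a shift; it is no evidence that a shift will occur.

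**The case against.** The strongest reply is that the text never says DHI, VAS-V and VAS-T are taken after randomisation. The sentence on timing covers demographic and clinical characteristics, most of which allocation can hardly alter. The scores come in a separate sentence that sets baseline apart from the weeks after randomisation. Much of what the paragraph calls baseline is eligibility work, and a single baseline visit includes consent. The paragraph may therefore be a list and not a sequence. The flow diagram and the schedule of assessments (Fig. 1 and Table 3) are not reproduced in the copy reviewed and may fix the order.

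Much of this stands. The timing of the self-reported scores is an inference, and the missing displays are no fault of the plan. But the order stated for the history, including initial symptoms, remains, and no visible text places the scores earlier. If the displays do so, the prose still needs to agree with them.

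It is also fair that follow-up self-reports are unblinded in any case. A reporting shift of equal size at baseline and follow-up would cancel in a change score. The added and avoidable problem is a reference value affected on its own.

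**Conclusion.** The point holds as a badly fixed sequence affecting self-reported secondary outcomes and the baseline symptom history. As written, the reference scores may be recorded when the patient knows the arm or has begun treatment. The size and direction of any bias cannot be derived from the document; the error rates above rest on assumed shifts and correlations.

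Two stronger conclusions that a reader might infer are not supported:

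- **That the primary outcome is compromised.** The vestibular tests must precede randomisation to establish eligibility, and their assessors are blinded.
- **That covariate adjustment in general conditions on post-allocation variables.** The covariates named in the statistical methods are age, initial PTA, number of involved vestibular organs and MRI result. These are fixed, objective or tied to eligibility. Only the open reference to other characteristics could admit a self-reported item.

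**What to change.** Reconcile Participants, Recruitments and randomization, and Time points with one statement, for example: *Consent, eligibility tests, baseline history, PTA, DHI, VAS-V and VAS-T are all completed before the allocation envelope is opened.* Remove the wording that puts baseline collection after randomisation, and check that Fig. 1 and Table 3 show the same order. Add that any self-reported baseline item recorded after allocation is flagged in the data.

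The cost is one or two sentences and, at most, a different order of steps at the same visit. Sample size, treatment and follow-up schedule are unchanged. If recruitment has begun, record which patients completed their baseline scores after allocation.

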### Interventions and comparisons

Once a participant is randomized, the treatment procedure starts immediately (Table 1). The participants in group 1 will receive oral prednisone 1 mg/kg/day (maximum daily dosage is no more than 60 mg) for 7 days, followed by a 7-day taper (Table 1). The patients are advised to take the medicine in 30 min before every breakfast, and not to divide the doses. The participants in group 2 will receive 7 intratympanic 40 mg/ml methylprednisolone injections in 14 days, one injection every other day.

**Table 1 Tab1:** Glucocorticoid therapy protocol in each group

	Drug	Protocol
Group 1	Pred.	Glucocorticoid therapy: d1–d7: Oral Pred. 1 mg/kg/d (maximum daily dosage is no more than 60 mg) d8–d9: Oral Pred. 10 mg less than d7 d10–d11: Oral Pred. 10 mg less than d9 d12: Oral Pred. 10 mg less than d11 d13: Oral Pred. 10 mg less than d12 d14: Oral Pred. 10 mg less than d13^a^
Group 2	Met.	Glucocorticoid therapy: One intratympanic injection of 40 mg/ml Met. at d1, d3, d5, d7, d9, d11, and d13;^b^

Pred. prednisone, Met. methylprednisolone, d. day

^a^If the patient’s weight is less than 50 kg, the administration will be stopped after the day with < 10 mg prednisone administered, for example, a patient weighs 45 kg will stop receiving glucocorticoids at the 13th day

^b^One day early or late of injection is allowed for practicality

The otolaryngologists in charge of the injection work are asked to inject at the posterior superior quadrant and fulfill the tympanic cavity using operating microscopes, after lidocaine spray anesthesia. Patients will be asked to keep supine position with the affected ear slightly up to 30° and avoid swallow during injection and in 30 min after the injection. The drug for injection is methylprednisolone sodium succinate for injection by Pfizer Manufacturing Belgium NV.

Of all the participants, the length of treatment would be extended for another week if the change in hearing threshold (average dB in PTA) is less than 10 dB, or average of PTA is worse than 55 dB in the patient’s affected ear, under the participant’s agreement. The salvage treatment regimen is 3 injections of 40 mg/ml methylprednisolone every other day. Records and effects of the salvage treatments will be reported in the study results and evaluated according to both intention-to-treat (ITT) and per-protocol analyses. For those with severe vertigo attacks, drugs for symptom control like mannitol or diazepam can be used temporarily.

